## 7.2 Dosage, administration method and administration duration

### 7.2.1 Dosage

Initial dosage of nafamostat mesilate is 20mg per hour and will be adjusted between 10 to 30mg per hour upon the researcher's opinion.

### 7.2.2 Administration method

#### (1) Priming

Two vials of IV futhan is dissolved in 2mL of 5% glucose fluid and then added to 500mL of normal saline. This fluid was used to cleanse and charge the circuit.

#### (2) Extracorporeal circuit

One vial of IV futhan 50 was dissolved in 15mL of 5% glucose fluid. The mixture was continuously infused to the circuit in rate of 20mg per hour.

### 7.2.3 Administration duration

Futhan fluid was administered during CRRT duration

### 7.3 CRRT method

During CRRT, blood flow was maintained at the speed of 130 ~ 200mL/min, and was adjusted considering patient's condition.

### 7.4 Combination criteria

#### 7.4.1 Possible combination medication

The medications listed as following are possible to be used in combination with nafamostat mesilate during clinical study.

- ① The medication that was administered to the patients before the clinical study to manage underlying disease and does not temper with the result of the clinical study will be allowed under the researcher's approval.
- ② The transient medication to treat other disease and adverse events will be allowed under the researcher's approval.

The information (medication name, purpose, dosage, duration etc.) of all combination medication (including medications to treat other disease and adverse events) will be thoroughly reported in the patient's case report.

#### 7.4.2 Medication that are prohibited to use in combination

The medications listed as following are not allowed to use in combination with nafamostat mesilate.

- ① Medication in similar effect: warfarin, urokinase, FOY, aprotinine, dextrin, prostaglandine etc.

② Anticoagulation medication: heparin, citrate, hirudine etc.

When the patient is needed to use medication that are prohibited to use in combination with nafamostat mesilate under researcher's approval, the patient is excluded from the study immediately and an accurate and detailed documentation should be noted at the last page of the clinical report.

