## 4. Medications in clinical study

### 4.1 Overview of study medication

#### 4.1.1 Study medication

- Name: Futhan IV
- Active principal: nafamostat mesilate
- Dose: nafamostat mesilate 10 or 50mg/vial
- Character: white powder in clear vial
- Storage: at room temperature (1~30℃)
- Volume of active principal
  - 10mg of nafamostat mesilate in IV futhan
  - 50mg of nafamostat mesilate in IV futhan 50
- Effect:
  - ① Relieve acute symptom of pancreatitis (acute pancreatitis, acute phase of chronic pancreatitis, post-Op acute pancreatitis, acute pancreatitis after pancreatic duct imaging, traumatic pancreatitis)
  - ② Disseminated intravascular coagulation
  - ③ Anticoagulation of extracorporeal circuit on patients with hemorrhagic disease or tendency
- Dosage
  - (1) Administration
    - ① To relieve acute symptom of pancreatitis
      - : Generally, 10mg of nafamostat mesilate is dissolved in 500mL of 5% glucose fluid and administered intravenously for 2 hours once or twice daily. Decrease or increase on symptom.

② DIC

: 0.06~0.20 mg/Kg of nafamostat mesilate is dissolved in 1,000mL of 5% glucose fluid and administered intravenously for 24hours continuously.

③ To anticoagulate the extracorporeal circuit on patients with hemorrhagic disease or tendency

: For priming, two vials of nafamostat mesilate were dissolved in 2 mL 5% glucose fluid and mixed with 1000 mL normal saline. After carefully removing air bubbles from the circuit with the prepared fluid, nafamostat mesilate was dissolved with 15 mL of 5% glucose fluid and loaded into the anticoagulation line with a starting dose of 20~50 mg/hr. In clinical study, average dose of maintenance was 35mg/hour.

(2) Making IV fluids

To properly administer nafamostat mesilate, IV fluid should be prepared in following order.

① To relieve acute symptom of pancreatitis

① Add more than 1mL of 5% glucose fluid in 10mg nafamostat mesilate vial and dissolved fully.

② Mix fully dissolved fluid into 500mL of 5% glucose fluid.

② DIC

① Add more than 1mL of 5% glucose fluid in 10mg vial and more than 5mL of 5% glucose fluid in 50mL vial until fully dissolved.

② Mix fully dissolved fluid into 1,000mL of 5% glucose fluid.

③ To anticoagulate the extracorporeal circuit on patients with hemorrhagic disease or tendency

① For priming

i ) Add more than 1mL of 5% glucose fluid in 10mg vial and more than 5mL of 5% glucose fluid in 59mL vial until fully dissolved.

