## 6. Inclusion/exclusion criteria, target number of subjects and its estimation basis

### 6.1 Inclusion criteria

Patients are selected as subjects with following conditions;

- (1) Adult male/female patients aged from 18 to 80.
- (2) ICU patients who are hemodynamically unstable to be in need of CRRT and has one of the hemorrhagic tendencies described as follows.
  - ① Platelet < 100,000
  - ② aPTT > 60 sec
  - ③ PT-INR > 2.0
  - ④ Active bleeding
  - ⑤ Major surgery within 48 hours
  - ⑥ History of cerebral hemorrhage or major bleeding within 3 months
  - ⑦ Septic shock or DIC
- (3) Patients or his/her legal guardian has voluntarily agreed to participate in the study and provided written informed consent.

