## 10. Study discontinuation, drop out, or analysis exclusion criteria

## 10.1 Study discontinuation and drop out criteria

All patients who enrolled in the study should be recorded of the completion of the study, and if the medication is discontinued or observation is stopped, the reason is recorded. The criteria for patient's drop-out are as follows.

- ① Circumstance that violates inclusion/exclusion criteria
- ② Serious adverse events occurred in patients or patients demands to be dropped out of the study due to adverse events.
- ③ Patient or legal guardian demand the discontinuation of the study due to unsatisfactory curative value during the study.
- ④ Severe hemorrhage
- ⑤ Critical violation of study protocol by principal investigator, researcher or patients.
- ⑥ Patients or legal guardian's withdrawal of the consent.
- ⑦ When patients cannot be followed.
- ⑧ When the patient takes a medication that can influence the study result, without the researcher's authorization during study period.
- ⑨ When the patient is decided not fit for the study progression by researchers.

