## 10.2 Disposal of violation on protocol and non-compliance

The principal investigator and researchers should fully recognize and perform the study protocol, hence the protocol is not violated. However, the inevitable violation will be dealt with as follows.

In case of severe protocol violation, researcher should disregard the patient's data from the analysis and the criteria are as follows.

- ① Failure to acquire written consent
- ② Violation of inclusion/exclusion criteria
- ③ Administration of the medication that is prohibited to use in combination during the study.

Other violation of protocol that is decided to be minor and is not thought to influence the study analysis is thoroughly documented with the degree of violation, reason. Afterwards, the violation is evaluated by researcher, funder, monitor, statistician whether the violation has tempered with the study and included in the PP analysis.

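### The prohibited-medication rule and its immediate exclusion are worded only for nafamostat recipients. No explicit rule covers anticoagulant use in the no-anticoagulation arm, so removal from the principal per-protocol analysis can depend on the arm.

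*Protocol*

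**What the plan says.** **Permitted and prohibited drugs.** Section 7.4.1 lists medication that is "possible to be used in combination with nafamostat mesilate during clinical study". Section 7.4.2 opens with "The medications listed as following are not allowed to use in combination with nafamostat mesilate" and lists drugs of similar effect (warfarin, urokinase and others) and "Anticoagulation medication: heparin, citrate, hirudine etc". If a patient needs a drug prohibited in that sense under the researcher's approval, "the patient is excluded from the study immediately".

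**Removal from the analysis.** Section 10.2 says the data of a patient with a severe violation are to be disregarded. Item 3 of its list is "Administration of the medication that is prohibited to use in combination during the study". It names no arm.

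**Drop-out criteria.** Section 10.1 applies to all enrolled patients. Item 8 reads "When the patient takes a medication that can influence the study result, without the researcher's authorization during study period". Item 5 is critical violation of the protocol by investigator, researcher or patient. Item 9 is a decision by the researchers that the patient is unfit to continue.

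**Comparator and analysis sets.** The control arm is a no-anticoagulation group (7.5), and the trial is open label (4.3). Section 11.3.1 makes the per-protocol (PP) analysis principal for efficacy and the ITT analysis additional. The PP set is the patients who successfully concluded the protocol. The ITT set requires that the patient is known to be alive or dead.

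**Nafamostat.** Section 4.1.1 gives "Disseminated intravascular coagulation" as one of its indications, and section 6.1 admits patients with "Septic shock or DIC".

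**The concern.** The comparison is nafamostat against no anticoagulant. The event that most directly erodes it is an anticoagulant given to a control patient, for instance because filters keep clotting. The protocol makes this foreseeable: section 3.2 names several alternative anticoagulation methods used in patients with a bleeding tendency, and section 8.2.8 records filter clot as a reason for failure.

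The rule is nevertheless written around combination with nafamostat, a condition that a control patient does not meet. A futhan patient who needs a listed drug leaves the study automatically. A control patient given the same drug leaves only if someone who knows the allocation decides that it was a critical violation.

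Two distortions can follow in the principal analysis:

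- One-sided removal leaves a futhan PP set selected for patients who did not need rescue.
- Treated controls who are kept dilute the contrast in mortality, filter life, bleeding and transfusion.

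**Working it through.** **Step 1. The plan's own figure.** Section 6.3.2 uses n = Z²p(1−p)/δ² with α = 0.10 two-sided (Z = 1.645), p = 0.50 and δ = 0.15:

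- 1.645² × 0.25 / 0.0225 = 30.06, rounded up to 31.
- 31 / 0.95 = 32.6, rounded up to 33.

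Both match the protocol. The allowance is 33 − 31 = 2 patients per arm. Here δ is a precision margin for one proportion. It is not a planned difference between arms.

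**Step 2. One event, two arms.** Suppose the researcher approves a listed anticoagulant for one patient in each arm.

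| Clause | Futhan patient | Control patient |
|---|---|---|
| 7.4.2 | Condition met; immediate exclusion | Condition (combination with nafamostat) not met as worded |
| 10.2 item 3 | Data disregarded | Unclear: no arm named, but the list it relies on is the one in 7.4.2 |
| 10.1 item 8 | Not needed; already excluded | Not triggered, since the use was authorised |
| 10.1 items 5 and 9 | Not needed | Can apply, by judgment; critical is not defined |
| 11.3.1, PP set | Out | Depends on whether the protocol is judged successfully concluded |

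The futhan column is settled by rule. The control column rests on discretion at every step.

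**Step 3. Nafamostat outside the assigned treatment.** Nafamostat is not named in the 7.4.2 list. DIC is both an indication (4.1.1) and an entry criterion (6.1). The protocol does not say how to classify nafamostat given to a control patient, or a separate systemic course in a futhan patient.

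**Step 4. The ITT analysis may not repair this.** Exclusion under 7.4.2 is from the study, and 10.2 does not say which analysis the data are dropped from. The ITT set needs a known vital status. If an excluded patient is no longer followed, that patient can be lost from both analyses.

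**Step 5. Possible scale, with assumed inputs only.** The protocol gives no rescue rate, so these are illustrations.

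*One-sided removal.* Take 33 futhan patients with 50% mortality (the value in 6.3.2). Remove m of them, whose mortality is assumed to be q. The rest have mortality (33 × 0.5 − m × q)/(33 − m).

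| m | q = 0.7 | q = 0.3 |
|---|---|---|
| 2 | 15.1/31 = 48.7% | 15.9/31 = 51.3% |
| 4 | 13.7/29 = 47.2% | 15.3/29 = 52.8% |
| 6 | 12.3/27 = 45.6% | 14.7/27 = 54.4% |

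The shift is 1.3 to 4.4 points, in either direction.

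*Dilution.* Suppose a fraction c of controls receive a drug with the full effect of nafamostat and are kept. Any true difference is then multiplied by 1 − c: 0.90, 0.80 and 0.70 for c = 0.10, 0.20 and 0.30.

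**The case against.** The strongest reply is that silence in a list of drugs not to be combined with nafamostat is not permission. The control arm is defined as no anticoagulation, and the population is patients in whom heparin is ruled out. Giving such a patient an anticoagulant departs from the assigned treatment. Section 10.1 item 5 is arm-neutral and has no exception for authorised use, and the PP set is limited to patients who successfully concluded the protocol. This stands. A reader might infer that control patients are allowed these drugs and simply stay in the trial, or that no clause could catch them. The documents support neither reading.

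The nafamostat wording may also be loose drafting for study treatment. Section 7.4.1 is worded the same way, and read literally it would leave controls with no permitted-drug rule at all. That is plausible, but it makes the text ambiguous without settling it.

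On nafamostat for DIC, trial stock is labelled for the study only (4.2, 14.9), and its absence from a list of drugs not to be combined with itself is no surprise. This also stands. The remaining point is narrow: the protocol gives such use no classification.

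Finally, a reader might treat the 15% in 6.3.2 as a treatment effect that contamination would shrink. It is a precision margin, so no loss of a planned effect can be derived from it. Nor does the drop-out allowance show a shortfall in itself, since the loss of two patients leaves exactly the planned 31.

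What the reply does not answer is the asymmetry. Exclusion is automatic in one arm and discretionary in the other, among staff who know the allocation.

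**Conclusion.** The concern holds as a defect in how the rule is fixed. As written, 7.4.2 and 10.2 item 3 give a mandatory exclusion tied to nafamostat use, and no explicit rule covers anticoagulant use or crossover to nafamostat in the control arm. Because PP is the principal efficacy analysis and the trial is open, following the text can produce arm-dependent exclusion from the analysis that carries the conclusion. That goes beyond missing detail.

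The size and direction of any bias cannot be computed, since neither a rescue rate nor the prognosis of rescued patients is given. The ranges under working rest on assumed inputs and show only that a few exclusions matter with 33 patients per arm. The conclusion depends on reading 7.4.2 as worded. If the sponsor meant it for both arms, the text still has to say so.

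**What to change.** - Reconcile 7.4.1, 7.4.2, 10.1 and 10.2 so that one concomitant-medication rule, with the same consequence, applies to both arms from randomisation to the end of CRRT. Make 10.2 item 3 refer to that two-arm rule.
- Classify anticoagulant use in controls, and nafamostat given outside the assigned treatment in either arm, as recorded deviations with drug, time and reason.
- Keep every such patient in follow-up for ICU and 28-day vital status and in the ITT analysis, instead of excluding them from the study.
- Leave to the sponsor which drugs are clinically acceptable. The request is only that the passages agree and treat both arms alike.

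The cost is wording. Concomitant drugs and medication changes are already recorded (7.4.1, 8.2.11), and mortality at discharge and at 28 days after the start of CRRT is already collected (8.2.15, 8.3.4). The small downside is that more control-arm deviations will be counted.

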## 7.5 Randomization

In this study, patients are randomly assigned to either futhan group or no-anticoagulation group and are proceeded as parallel study. Necessary subject number is 33 patients in each group, considering the wastage rate of 5%.

At the enrollment, patients are assigned randomly with stratification of diabetes mellitus. Patients who enrolled in the study was assigned to futhan group or no-anticoagulation group according to the random assignment number by preformed random place card.

If group A is futhan group, group B is no-anticoagulation group, vice versa.

The following is the example when block size is 4 or 6

List number of cases: 1=AABB, 2=ABAB, 3=ABBA, 4=BAAB, 5=BABA, 6=BBAA, 7=AAABBB, 8=AABABB, ..., 26=BBBAAA (26 number of cases)

SAS Random Program value (randomly assign 1 to 26): 1, 26, 8, 2, 1 ....

Random assignment order: AABB BBBAAA A ABABB ABAB AABB ....

Random assign number of subjects was assigned to the patients who fit the inclusion criteria and not the exclusion criteria in order of registration by the random place card that was pre-distributed to the researchers

## 8. Observation, clinical examination and observation method

### 8.1 Clinical study schedule

| Period                                        | Screening | Treatment  | Closing  | Follow-up  |
|-----------------------------------------------|-----------|------------------------|----------------------|------------------------|
| Written consent                               | X         |                        |                      |                        |
| Authorize a Screening number                  | X         |                        |                      |                        |
| Demographical analysis                        | X         |                        |                      |                        |
| Personal/Drug history survey                  | X         |                        |                      |                        |
| Vital sign check                  | X         | X                      | X                    |                        |
| Physical examination                          | X         |                        | X                    |                        |
| Pregnancy test                    | X         |                        |                      |                        |
| Clinicopathologic examination     | X         | X          | X                    |                        |
| Severity analysis                             | X         |                        |                      |                        |
| Filter life span                              |           | X                      | X                    |                        |
| CVP monitoring                                |           | X                      |                      |                        |
| Subject compatibility assessment  |           | X                      |                      |                        |
| Randomization                                 |           | X                      |                      |                        |
| Drug administration                           |           | X                      |                      |                        |
| Check difference in drug dosage               |           | X                      | X                    |                        |
| Adverse event check                           |           | X                      | X                    |                        |
| Residual renal function check     |           |                        |                      | X                      |
| Mortality check                               |           |                        | X                    | X                      |
| Blood loss                                    |           | X                      | X                    |                        |
| Packed RBC transfusion                        |           | X                      | X                    |                        |
| Free frozen plasma, Platelet      |           | X                      |                      |                        |

1: administered until treatment is concluded

2: If patients are improved, closing examination was performed at discontinuation of CRRT. However, if the patient has deceased, the last examination before death was used.

3: Body temperature, pulse rate, respiratory rate, blood pressure was examined before other examination was performed. During CRRT, vital sign was examined every 4 hours. At screening, body temperature was examined rectally.

4: Pregnancy test was performed in female without sterilization or any effective contraception in child-bearing age.

5: Detailed examination was as following;

- Hematologic: Hemoglobin, Hematocrit, RBC, WBC, Platelet, differential count, ESR
- Biochemical: Alkaline phosphatase, BUN, Creatinine, SGPT (ALT), SGOT (AST), Total bilirubin, Uric acid, Na, K, Cl, Ca, P, CRP, total CO2
- Arterial Blood Gas: O2, CO2, arterial pH, HCO3, Base excess/deficit, Oxygen saturation
- Lipid: Cholesterol
- Urine analysis: pH, Protein, Glucose, Ketone, WBC, RBC
- Coagulation test: aPTT, PT-INR
- Specific coagulation test: fibrinogen, fibrin degradation product

During CRRT, Clinicopathologic examination was performed every 72 hours. If CRRT was discontinued before 72 hours, examination was performed at discontinuation. Uine analysis was performed at screening and closing. Specific coagulation examination was substituted for the examination performed recently

6: Subject compatibility assessment was performed based on all examination, personal history and inclusion/exclusion criteria. Patients who were fit in these criteria was enrolled as subjects.

7: The patients were followed until discharge for mortality to confirm survival until 28 days after initiation of CRRT.

8: After discontinuation of CRRT, patients were followed at discharge to confirm dialysis maintenance and at first outpatient department follow-up after discharge, renal functional restoration was checked.

9: Free frozen plasma, platelet transfusion was checked during CRRT.

## 8.2 Observation

### 8.2.1 Written consent and demographical survey

Before clinical study begins, the patients are thoroughly explained about the purpose and content of the clinical study and after patients sign the consent form, screening number is assigned and demographic survey is sought.

Record data is approval or disapproval, approval date, initial of subject, sex, birth date, age, etc.

### 8.2.2 Past history and drug history survey

Patient's past medical history and medication administered to the patient within 4 weeks is thoroughly identified by examining patient's medical examination and check medical history. The contents that need to be included are as following;

Past medical history including surgical history, allergy etc. for the past 2 years, duration of current diseases (year or year and month at which the disease has occurred; has to investigate thoroughly by interview), researcher's remark,

#### 8.2.3 Vital sign

Vital sign includes body temperature, pulse rate, respiratory rate, and blood pressure. Vital sign is checked right before and initiation of CRRT and continued afterwards every 4hours. Body temperature was checked rectally at screening.

